### B1. PURPOSE OF PROTOCOL

The purpose of this study is to investigate the effects of a) a homeopathic supplement marketed for heartburn symptoms (Acidil) and b) components of the placebo response (the doctor-patient interaction and belief/expectation) on symptoms and health-related quality of life (HRQL) in patients with gastroesophageal reflux disease (GERD). This study is designed as a pilot trial to assess safety and feasibility and to provide preliminary estimates of effect sizes in anticipation of conducting a larger trial in the future.

**Aim 1:** To determine the safety and feasibility of conducting this 2x2 factorial design randomized controlled trial in this patient population.

**Hypothesis 1:** This study design will be both safe and feasible and subject recruitment will not be difficult (i.e., no significant adverse events and greater than 90% of those who enroll will complete the study protocol).

**Aim 2:** To determine whether changes in GERD-specific, dyspeptic, and overall symptoms and HRQL are significantly different between subjects receiving Acidil and subjects receiving an identical placebo.

**Hypothesis 2a:** Compared to subjects receiving placebo, more subjects receiving Acidil will experience a 50% or greater improvement in GERD symptom severity during the last 7 days of the study compared to baseline.

**Hypothesis 2b:** The dynamic trajectory of symptom changes over time will differ between the Acidil and placebo groups as expected according to homeopathic theory.

**Hypothesis 2c:** Subjects receiving Acidil will report greater improvement in disease-specific and overall quality of life compared to the placebo group.

**Aim 3:** To determine whether changes in GERD-specific, dyspeptic, and overall symptoms and HRQL are significantly different between subjects receiving an expanded clinical interview similar to a homeopathic consultation (enhanced physician-patient interaction) vs. a standard allopathic interview, and to determine whether any treatment responses are mediated by preconceived beliefs and expectations regarding treatment efficacy.

**Hypothesis 3a:** Compared to subjects receiving the standard clinical interview, more subjects receiving an expanded clinical interview will have a 50% or greater improvement in GERD symptom severity during the last 7 days of the study compared to baseline.

**Hypothesis 3b:** Subjects receiving an expanded clinical interview will report greater improvement in disease-specific and overall quality of life compared to subjects receiving a standard clinical interview.

**Hypothesis 3c:** Subject beliefs and expectations pre-treatment will partially explain changes in GERD and dyspeptic symptoms in the expanded vs. standard interview groups but not in the Acidil vs. placebo groups.

## **B2. SIGNIFICANCE AND BACKGROUND FOR THE STUDY**

### **Gastroesophageal Reflux Disease (GERD)**

Twenty to thirty percent of Americans experience GERD-related symptoms consisting of heartburn and/or acid reflux at least weekly (1). Although proton pump inhibitors (PPIs) are the third largest class of pharmaceutical drug sales in the United States (2), there is increasing concern about the overuse and negative side effects of these medications. A growing body of evidence has linked PPI use with increased risk of *C. difficile* infections, small bowel bacterial overgrowth, osteoporosis, nutritional deficiencies, and potential drug-drug interactions related to CYP450 enzyme metabolism (2, 3). Moreover, many patients continue to experience distressing GI symptoms despite taking PPIs. A number of these patients have functional heartburn symptoms and/or co-occurring dyspeptic symptoms (e.g., upper abdominal discomfort, bloating, and gas) that do not respond well to this class of medication (4).

### **Placebo Response**

A review of placebo-controlled PPI trials suggests that the magnitude of the placebo response in patients with GERD averages around 19% (range 3-47%, (5)). However, the factors that influence the magnitude of this response in this patient population are poorly understood. Data from studies of other conditions suggests that the placebo response is a complex phenomenon that includes: natural history & regression to the mean, expectancy & belief (involving both the patient and the doctor), classical conditioning, learning, and reward pathways in the brain, and the quality of the therapeutic encounter & ritual (6, 7). Recent work by [name], [name], and colleagues has demonstrated that in patients with irritable bowel syndrome, the magnitude of the placebo effect can be augmented by enhancing the quality of the therapeutic interaction (7) and that a genetic polymorphism in the catechol-o-methyltransferase gene correlates with this response (8). To date, there have been no studies examining the components of the placebo response in patients with GERD.

### **Complementary Medicine**

Many patients are interested in exploring alternative treatments for their medical conditions aside from traditional pharmaceutical drugs. In 2007, 38% of US adults had used some form of complementary medicine and spent \$33.9 billion out-of-pocket on practitioner visits and over the counter (OTC) products (9). The majority of these OTC products have not been formally tested for safety or efficacy. The same survey also revealed that homeopathy is one of the top 10 complementary modalities used in the US, with the population spending nearly \$2.9 billion out of pocket on homeopathic medicines and services.

### **Homeopathy**

Homeopathy is a system of medicine that was founded in 1796 by the German physician Samuel Hahnemann. It has grown to become one of the most popular medical systems used across the world (10). Indeed, the Swiss government recently reviewed the evidence for homeopathy and concluded that

there was sufficient data regarding safety, efficacy, and cost-effectiveness to warrant coverage of homeopathic services by the national health system (11).

Nonetheless, some authors believe that the effects of homeopathy are due to enhanced placebo effects and an augmented doctor-patient interaction. In classical homeopathy, a typical homeopathic consultation can last 1-2 hours and involves the exploration of domains of illness not usually discussed in a typical allopathic medical consultation. These extensive consultations are deemed necessary to gather adequate information to properly individualize a patient's treatment, a process that is complex and labor intensive.

To make homeopathy more accessible to the lay public, some homeopathic pharmaceutical companies have created formulations for common conditions that combine multiple homeopathic medicines commonly used to treat a set of symptoms into a single product, or supplement, marketed to treat a specific indication (e.g., heartburn, insomnia, or seasonal allergies). While combination homeopathic products do not conform to the standards of classical homeopathy (in which only a single homeopathic medicine is prescribed at a time and typically higher dilutions are used), they are widely sold over the counter in the U.S. and used by the public to treat a variety of conditions. The efficacy of many of these products has not been verified in the peer-reviewed literature.

To date, there are no trials of homeopathy specifically for the treatment of GERD, however, homeopathic providers often prescribe for GERD-related symptoms (personal communication). There are trials suggesting possible benefit of individualized homeopathy for dyspeptic symptoms (12) as well as functional medical conditions such as fibromyalgia (13).

Homeopathic medicines are generally regarded as very safe, due to the low concentrations of active ingredients present, with adverse event rates generally estimated to be 3% or less and serious adverse events extremely rare (11, 14). In the United States, homeopathic medicines are regulated by the FDA under the 1938 Food, Drugs, and Cosmetics Act (15). The majority of homeopathic medicines are available OTC without a prescription required. According to the manufacturer (Boiron) of the product to be used in this study (Acidil), there have been no adverse event reports for this supplement over the last 10 years in the United States.

Despite the relative safety of homeopathic medicines, certain types of treatment reactions are commonly recognized by the homeopathic community. These include aggravations and provings. An aggravation is a transient aggravation of a patient's symptoms followed by a marked improvement in symptoms and is felt to be a positive prognostic sign of healing. A proving occurs when a patient manifests symptoms that the homeopathic medicine is designed to treat and usually occurs when a patient has received too much of the medicine and/or the medicine is poorly matched to the patient's symptoms. Aggravations and provings may explain the dynamic oscillations seen in patients' symptoms in the homeopathy arms, but not the placebo arms, of some randomized controlled trials (16, 17). These observations complicate the interpretation of treatment outcomes and may account for some inconsistent results in prior homeopathic studies. Thus, in our study, we propose to monitor dynamic changes in symptoms over time as well as conduct endpoint analyses.

### B3. DESCRIPTION OF RESEARCH PROTOCOL

#### A. Study Design – Overview, Methods, Procedures

##### Overview

We propose to conduct a single-center, pilot feasibility, 2x2 factorial design randomized controlled trial assessing the effect of a homeopathic supplement (Acidil) and components of the placebo response (doctor-patient interaction and beliefs/expectations) on symptoms and HRQL in patients with GERD over a 2 week time interval. The Acidil vs. placebo intervention will be double-blinded and the standard vs. expanded interview intervention (doctor-patient interaction) will be single-blinded. Randomization will be by permuted block randomization with block sizes of 4 and 8. We plan to enroll 6 patients into each group for a total of 24 subjects in the study according to the adjacent scheme. Subjects will be evaluated in the GCRC at BIDMC at two timepoints: baseline and at 2 week follow-up.

|                    | Acidil  | Placebo |
|--------------------|---------|---------|
| Standard Interview | Group 1 | Group 2 |
| Expanded Interview | Group 3 | Group 4 |

##### Detailed Study Procedures, Timeline, Testing, and Outcome Measures

An overview of the study timeline is shown below.

**Figure 1: Study Timeline**

[figure not shown]

x = daily symptom severity and frequency and medication use diary

##### Telephone Screening (Time 0: -1.5 to -3 weeks):

When a potential study subject calls to inquire about participating in the study, they will be provided with further information over the phone (Appendix A) about the study and their questions answered. If they are interested in participating, potential subjects will undergo a brief telephone screen to assess eligibility (Appendix A). If they are a BIDMC patient, their OMR record will be reviewed to confirm eligibility. If they pass the telephone screen, they will be informed that they are likely eligible for the study, but will need to complete a baseline symptom diary and have a final in-person eligibility assessment at BIDMC. If they wish to proceed, instructions for completing the baseline symptom diary

will be explained, a diary will be mailed to the potential subject, and appointments scheduled for a baseline evaluation and 2 week follow-up. Potential subjects will be called several days after the diary is mailed to ensure that they received it and that the instructions for completing the diary are clear.

#### First Study Visit (Time 1):

When a potential subject arrives at the study site, the diary will be reviewed to ensure that it meets eligibility criteria (symptoms at least 3 days out of 7 and symptom frequency and severity recorded on at least 6 days of 7) and the individual will undergo a final in person eligibility assessment reviewing the criteria discussed during the phone screen. Subjects deemed ineligible will be thanked for their effort, informed that they are not eligible, receive parking validation and be dismissed.

Eligible subjects will be formally consented, have blood drawn (if they opt to participate in the repository study described in a separate application), and complete a series of baseline questionnaires (demographics, medication and supplement use, GSRS, Nepean Dyspepsia Index, GERD-HRQL, SF-12, MYMOP, credibility questionnaire, CAMBI, see Table 1 below). Next, subjects will be randomized to one of the 4 treatment groups and receive either the standard or expanded interview in a single-blinded fashion (the study physician will be aware of assigned interview type, but the subject will not). The clinical interview will be audio and video recorded (pending subject permission) to permit subsequent assessment of fidelity to the treatment protocol.

After the interview, subjects will complete additional questionnaires (CARE, credibility questionnaire, see Table 1). Finally, subjects will receive the study medication (Acidil or placebo) in a double-blinded fashion (neither the study physician nor the subject will be aware of treatment assignment) and rescue antacid. The study physician, or another member of our research team, will provide medication education. All subjects will receive the same instructions for how to take the study medication and rescue antacid, will be provided with a new study diary, and their 2 week follow-up appointment will be confirmed. Study subjects will be contacted 7 days following the first study visit to confirm that they are taking the study medication, completing their daily diary, and not experiencing any marked adverse effects. The first study visit is anticipated to last 1-2.5 hours.

#### Intervention and Control Groups:

##### *Standard and Expanded Intake Groups*

Subjects assigned to groups 1 and 2 will receive a standard allopathic clinical interview (Appendix B) by the study physician inquiring into the nature and history of their GERD and dyspeptic (if present) symptoms and prior and current treatments undertaken to control symptoms, including any complementary treatments. The study physician will also review the subject's symptom diary and the study questionnaires completed immediately prior to the interview and conduct a brief physical exam. The interview is expected to last 20-30 minutes.

Subjects assigned to groups 3 and 4 will receive an expanded clinical interview (Appendix B) by the study physician similar to the type of interview performed by classical homeopathic physicians. In addition to the above evaluation, the expanded interview will also include questions inquiring about any additional symptoms or diagnoses that the subject currently has, the subject's temperament, likes and dislikes, effects of weather on symptoms, and sleep. The expanded interview is expected to last approximately 1 hour, though for medically complex patients it could last as long as 1.5 hours.

The same study physician ([name]) will be conducting all study interviews and thus will not be blinded to this aspect of study group assignment, but will remain blinded to study medication assignment. [name] has been receiving training in classical homeopathic case taking and analysis and will thus be able to mimic the types and depth of questions typical for a homeopathic consultation. As this aspect of the intervention is primarily about the length of time spent with the subject, and depth of questions asked, there will be no overt attempt to vary the amount of empathy between the two

interview types. However, we will be measuring perceived empathy using the CARE questionnaire. Engagement with a warm, caring provider is known to improve response to treatment ([name]). Whether consultation length affects treatment response and whether this effect is mediated through perceived empathy is unknown. Both the standard and expanded intakes will be audio and video recorded (physical exam component audio only so that the study camera does not need to be moved and to preserve subject modesty) so that they can be analyzed later by an independent evaluator to ensure fidelity to the study protocol. Consent for recording will be separate from the study consent so that a subject may still consent to study participation even if he/she declines audio and/or video recording.

At the time of consent, study subjects will not be informed about the two different interview types or that part of the study involves testing the effect of the doctor-patient interaction on response to treatment. Concealment of these aspects of the study protocol is essential to maintaining the validity of the study as data suggests that patients responses change when they know that the doctor-patient interaction is being studied (6, 18). Subjects will be informed in the consent document that their interview with the study physician could last anywhere from 20-90 minutes. We plan to notify subjects at the end of the study, after the exit interview, that there were two possible types of physician interviews, that this aspect of the study was concealed from them, and of the rationale for why we did so. A script outlining this planned debriefing is present in Appendix F. We believe that this aspect of the intervention is minimal risk and that our plan meets the federal criteria for permitting alteration of some elements of informed consent (19).

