**Hypothesis 3a:** Compared to subjects receiving the standard clinical interview, more subjects receiving an expanded clinical interview will have a 50% or greater improvement in GERD symptom severity during the last 7 days of the study compared to baseline.

We will perform an analysis analogous to that for hypothesis 2a above by combining responses to the daytime heartburn, nighttime heartburn, and acid regurgitation questions for the last 7 days of the study compared to baseline on the daily symptom dairies comparing groups 1 + 2 with groups 3 + 4 using a logistic regression analysis and including an interaction term for the two study interventions.

**Hypothesis 3b:** Subjects receiving an expanded clinical interview will report greater improvement in disease-specific and overall quality of life compared to subjects receiving a standard clinical interview.

We will compare GERD-HRQL, Nepean Dyspepsia Index, and SF-12 scores between the standard (groups 1 + 2) and expanded (groups 3 + 4) interview groups, incorporating an interaction term for the two main treatment effects, using ANOVA.

**Hypothesis 3c:** Subject beliefs and expectations pre-treatment will partially explain changes in GERD and dyspeptic symptoms in the expanded vs. standard interview groups but not in the Acidil vs. placebo groups.

We will perform a logistic regression analysis including subjects' pre-treatment belief in CAM and scores on the credibility questionnaire using greater than 50% improvement in heartburn symptom frequency or severity during the last 7 days of the study compared to baseline (based on the daily symptom dairies) as the outcome. Due to the small sample size, we will be unable to adjust for potential confounders.

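### The protocol does not keep the interviewing physician, who knows the interview arm, from seeing the belief and credibility scores that hypothesis 3c uses as predictors

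*Protocol*

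**What the plan says.** Under First Study Visit (Time 1) in the protocol, eligible subjects consent and then fill in a set of baseline forms that includes "GSRS, Nepean Dyspepsia Index, GERD-HRQL, SF-12, MYMOP, credibility questionnaire, CAMBI". They are next randomized and interviewed. Under Standard and Expanded Intake Groups, the standard interview is described, and the physician is also to go over the diary and "the study questionnaires completed immediately prior to the interview". The expanded interview builds on this: "In addition to the above evaluation, the expanded interview will also include questions inquiring about any additional symptoms". The same physician "will be conducting all study interviews and thus will not be blinded to this aspect of study group assignment".

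Hypothesis 3c in section B1 states: "Subject beliefs and expectations pre-treatment will partially explain changes in GERD and dyspeptic symptoms in the expanded vs. standard interview groups". The Data Analysis section tests it with a logistic regression of symptom response on "pre-treatment belief in CAM and scores on the credibility questionnaire". Directly after the interview, subjects complete the credibility questionnaire again, together with CARE. Items 7 and 8 of the Additional Exploratory Analyses compare CARE between interview arms and follow credibility over time by assignment.

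**The concern.** Aim 3 asks whether a longer, deeper interview improves outcomes and whether prior belief and expectation account for part of any response. That is easiest to interpret if what happens in the interview does not depend on the recorded belief scores. A physician who sees that a subject is sceptical may reassure or explain more; one who sees an enthusiast may engage differently. Neither need be deliberate. Interview content would then vary with baseline belief, and a link between belief and response would mix the subject's own expectation with the physician's reaction to it.

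The protocol's own reasoning makes this relevant. Its Placebo Response background counts the doctor's expectancy, as well as the patient's, among the components of the placebo response. It also withholds the product's name from subjects partly to keep shifting beliefs from blurring the interview contrast. Leaving the interviewer's access to belief scores open sits poorly with that care. A pilot meant to supply effect estimates for a larger trial could also carry the procedure forward.

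**Working it through.** No arithmetic applies; the check is to set the relevant statements side by side.

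1. **When the scores are collected.** First Study Visit lists the credibility questionnaire and CAMBI among the forms done before the interview. The Study Measures and Timepoints table agrees, marking both in column 1a.
2. **What the physician reviews.** The intake description covers the diary and the forms completed just before the interview. It names neither instrument and exempts none, so their inclusion follows from combining it with step 1.
3. **In which arms.** The expanded interview adds to the standard evaluation, so the review belongs to both.
4. **Who reviews.** One physician does all interviews and knows the interview type, though not the tablet assignment.
5. **How the scores are used.** CAM belief and credibility are the 3c predictors. I take the pre-interview credibility score to be the one meant, as the hypothesis concerns beliefs before treatment.
6. **What is measured next.** Credibility and CARE are completed immediately after the interview.

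From this sequence:

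- **Out of reach:** the baseline scores, which are recorded before the interview, and the allocation, which comes from permuted-block randomization.
- **Within reach:** the content of the interview and, through it, post-interview credibility, CARE and possibly symptom response.
- **Direction:** not determined. Extra reassurance for sceptics would flatten an association between belief and response; greater engagement with believers would steepen it.
- **Difference between arms:** possible, because the standard interview is expected to take 20-30 minutes and the expanded one about 1 hour (up to 1.5 hours for medically complex patients). Longer contact leaves more room to adapt.

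The stated safeguards do not close the route. The undertaking not to vary empathy overtly is an intention and cannot cover unconscious adaptation. The recordings for independent fidelity review are examined afterwards, and subjects may decline them. The interview guide in Appendix B is not in the text available and could narrow the review, but the protocol body does not.

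**The case against.** Several points on the other side are sound.

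- A reader might infer that the physician reads the belief forms before starting each interview. The text does not say so: the timing phrase describes when subjects complete the forms, and the review is listed within the evaluation beside the physical examination. Reading them during the interview leaves the same opening, but exposure is something the wording permits and not an event it schedules.
- A reader might infer that the comparison between interview arms is contaminated. The document does not support that. The review occurs in both arms, and the protocol defines the interview contrast chiefly by duration and depth of questioning. More room to respond to the subject is therefore partly the intervention itself, and a shift in CARE or credibility by that route is not clearly bias in the randomized contrast. Differential influence is a risk only.
- A reader might want to attach a size. With 12 subjects per interview arm, the standard error of a standardized mean difference is sqrt(1/12 + 1/12) = 0.41 SD, but the protocol gives no shift to set against it. Any figure in standard-error units would only restate an assumption.
- Both interviews ask about complementary treatments, and the expanded one also covers temperament and preferences. The physician will learn something of each subject's outlook whatever happens to the forms.
- The stakes are modest. Feasibility is the primary outcome, adequate power for treatment effects is not expected, and CARE and credibility are listed as other measures.

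These points limit the finding but do not remove it: the belief scores themselves are still open to the interviewer, and neither interview description calls for them.

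**Conclusion.** The point holds as an avoidable and unquantified risk. As written, the procedure lets an interviewer who knows the interview arm see the 3c predictors and respond to them. A 3c association could then partly reflect that response, and post-interview credibility and CARE could be affected, possibly more in the expanded arm. The conclusion rests on reading the review instruction as covering every form completed just before the interview, and on Appendix B not restricting it. It does not imply that baseline scores or randomization are compromised, or that the arms are shown to be biased. The repair is worth making because it is cheap and because later analysis could not recover how the physician used the scores.

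**What to change.** In Standard and Expanded Intake Groups, limit the physician's review to the symptom diary and the demographic, medication, symptom and quality-of-life forms. State that the credibility questionnaire and CAMBI are collected sealed by other research staff and withheld from the physician until that subject's second visit is complete; the physician may conduct the exit interview, so release before then would reopen the route.

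As a sensible extension, have the same staff collect the post-interview credibility and CARE forms. CARE is completed after the interview and so lies outside the review at issue, but the handling can be the same.

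The cost is a sentence or two of text and minor form handling. The physician keeps the diary and every form bearing on symptoms, treatment and quality of life.
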